## Abstract

*Background*: Small vulnerable newborns (SVNs), including those born preterm, small for gestational age, or with low birth weight, are at higher risk of neonatal mortality and long-term health complications. Early exposure to maternal vaginal microbiota and breastfeeding plays a critical role in the development of the neonatal microbiota and immune system, especially in low-resource settings like Burkina Faso, where neonatal mortality rates remain high. *Objectives*: The DenBalo study aims to investigate the role of maternal and neonatal factors, such as vaginal and gut microbiota, immune development, and early nutrition, in shaping health outcomes in SVNs and healthy infants. *Methods*: This prospective cohort observational study will recruit 141 mother-infant pairs (70 SVNs and 71 healthy controls) from four health centers in Bobo-Dioulasso, Burkina Faso. The mother-infant pairs will be followed for six months with anthropometric measurements and biospecimen collections, including blood, breast milk, saliva, stool, vaginal swabs, and placental biopsies. Multi-omics approaches, encompassing metagenomics, metabolomics, proteomics, and immune profiling, will be used to assess vaginal and gut microbiota composition and functionality, immune cell maturation, and cytokine levels at critical developmental stages. *Conclusions*: This study will generate comprehensive data on how microbiota, metabolomic, and proteomic profiles, along with immune system development, differ between SVNs and healthy infants. These findings will guide targeted interventions to improve neonatal health outcomes and reduce mortality, particularly in vulnerable populations.

## 1. Introduction

Preterm birth, low birth weight (LBW), and small-for-gestational-age (SGA) newborns, collectively referred to as small vulnerable newborns (SVNs), account for the majority of neonatal mortality and are at higher risk for adverse health outcomes [1]. Understanding the biological processes that influence their growth and survival is crucial for designing targeted interventions to improve neonatal and their long-term health outcomes, particularly in Burkina, where the neonatal mortality rate remains alarmingly high at 24.6 per 1000 live births in 2022 [2], with an intra-hospital mortality rate as high as 27.8% in the Hauts-Bassins region [3]. In this context, SVNs contribute to these mortality statistics, with LBW prevalence estimated at 8–11% [4,5], preterm birth rates at 5.4–5.7% [6], and SGA infants accounting for 27.9% of births [7].

The neonatal period, encompassing the first days and weeks of life, is a critical window for the establishment of key biological systems essential for growth, development, and adaptation to life outside the womb [8]. These systems include the gut microbiota and immune system, which play a crucial role in shaping long-term health outcomes.

Vaginal delivery is a key event that exposes neonates to maternal vaginal and intestinal microbiota, providing the first gut microbial inoculum [9,10,11,12,13]. These early colonizers are linked to changes in the gut’s protein composition and the metabolic environment, suggesting they play a foundational role in shaping the developing microbiome [14]. However, whether the assembly and maturation of gut microbiota differ based on delivery term and birthweight, and how this impacts infant growth and development, remains unclear.

Neonatal nutrition is another significant critical factor that influences both gut microbiota and immune function. Breastfeeding is a primary determinant of infant gut colonization after birth [15], initiating tropic priming of the newborn gut and providing essential immunological components [16]. Despite its importance, the interplay between neonatal microbiome and immune system development, particularly in the context of nutrition, has not been extensively studied. This gap is even more pronounced in SVNs, who are predisposed to health challenges such as gut dysbiosis caused by physiological immaturity and prenatal/postnatal factors (e.g., prenatal maternal illness, rapid delivery, antibiotic provision) [17] and immature immune systems with compromised innate and adaptive immunity, exacerbated by complications related to preterm birth [18]. However, studies showed that the colostrum from mothers of SGA neonates is compositionally similar to that of full-term neonates [19]. In contrast, colostrum from mothers of preterm newborns, who are often characterized as LBW due to prematurity [20], exhibits a distinct composition. It contains higher levels of protein, fat, free amino acids, sodium, and bioactive milk components, such as human milk oligosaccharides (HMOs), cytokines, and lactoferrin [21,22]. Despite these differences, the association between early milk composition and infant growth and development remains inadequately explored. Consequently, it is unclear which specific components are essential for fostering a healthy gut microbiota and supporting a robust immune system in infants [17,18,19,20,21,22].

The neonatal period is also marked by heightened vulnerability to infectious diseases, with neonatal infections contributing to 40% of mortality in children under five [23]. Early microbial colonization plays a vital role in shaping the immune system and providing protection against infections [24]. Studies have shown that the neonatal immune system undergoes rapid development in the first week of life, with long-term health implications [8,25,26]. However, the effects of SVN status on immune system development and the role of human milk and the gut microbiome in these processes remain poorly understood [18,27].

Major advances in systems biology have facilitated unbiased and integrated analyses of high-dimensional omics databases, equipping researchers with essential bioinformatic tools to explore the neonatal microbiome and immunome [8]. This progress paves the way for a transformative shift toward impactful research that examines the interplay between these biological systems and newborn nutrition, addressing critical gaps in our understanding of neonatal health.

The DenBalo study aims to investigate the role of maternal and neonatal factors, such as vaginal and gut microbiota, immune development, and the composition of human milk, in shaping health outcomes in SVNs and healthy infants in urban Burkina Faso. To achieve this, the project will pursue three main objectives:To independently describe and compare the gut microbiota, immune system, and breastmilk (collectively referred to as “bio-networks” in this protocol) in SVNs and healthy controls, the latter comprising full-term neonates of normal birth weight;To detail the assembly and development of these bio-networks at high resolution during the first days and weeks of life;To integrate these bio-network data using multi-omics systems biology approaches for comprehensive analysis.

## 2. Materials and Methods

### 2.1. Study Setting and Participants

The DenBalo study follows a multicenter, prospective cohort design conducted at three health and social promotion centers (CSPSand one medical center (i.e., four health centers) with a surgical unit (CMA) in the Dô Health District, Bobo-Dioulasso, Burkina Faso. These health centers were selected based on data from a previous study conducted by our research group on postnatal weight loss in newborns, which allowed for real-time assessment of birth rate and evaluated the CSPS staff’s capacity to manage research demands.

Initial sample size calculations were based on data from the health centers. A sample of 140 mother-infant dyads (70 SVNs and 70 controls) was targeted. These participants will be followed up until the infants reach six months of age. The recruitment process and follow-up schedule are outlined in Figure 1 and further described below.

### 2.2. Recuitment Procedure

The selection and inclusion of participants will proceed in three steps:***Step 1. Screening***

During routine antenatal consultations (ANC), women aged 15 to 45 years in their early third trimester, with a symphysial fundal height between 24 and 27 cm, will be screened for eligibility (see Table 1). Project midwives will explain the study objectives, obtain oral consent, and refer potential eligible women for an ultrasound at the CMA of Dô to confirm gestational age (GA).

**
*Step 2. Pre-inclusion*
**

In the third trimester, traditional fetal biometric parameters such as abdominal circumference, biparietal diameter, and head circumference become less accurate for estimating GA [1]. Instead, the combination of transcerebellar diameter (TCD and femur length (FL), with an accuracy of ±15.1 days compared to the gold standard, will be used to estimate GA [28].

Following ultrasound assessments, FL and TCD will be measured in duplicate (i.e., on different images) to estimate GA. Any difference between repeated measurements of more than ±1 week of GA (i.e., >1.8 mm for TCD or >0.24 mm for FL) will result in a mandatory third measurement on a new image [29]. The quality control criteria for TCD and FL assessments are shown in Table 2.

Gynecologists will visually assess the quality of their own images according to predefined criteria and rank them in descending order, from best to worst [i.e., 1st, 2nd, (and possibly 3rd)]. GA will be calculated using the Alliance for Maternal Newborn Health Improvement (AMANHI) formula based on two best measurements [29].
$$GA_{AMANHI}=e^{[\left(0.3825021\times \ln\left(TCD\right)+0.3321277\times \ln\left(FL\right)\right]}$$

Singleton pregnancies with GA between 24 and 29 weeks (6 days) will be eligible for pre-inclusion (Table 1). After pre-inclusion, at 33 to 3 weeks of gestation, a team of sociologists will visit the participant’s family/family-in-law to explain the high-frequency nature of the study and facilitate data collection. The study’s aims, methods, procedures, risks, and limitations will be thoroughly explained to the participants. Informed consent will be obtained, and a highly visible “green card” will be attached to the participant’s health booklet to facilitate identification at the CSPS.

**
*Step 3: Inclusion*
**

At 36 weeks of gestation, study staff will contact pre-included participants by phone to encourage them to present at the CSPS with their green card when labor begins. Participants should show their “green card” upon arrival for direct referral to the project midwife. The midwife will assess for membranes, as intact membranes are required for vaginal microbiota sampling. If the membranes are intact, newborns will be categorized into either the SVN group or the control group based on inclusion criteria (Table 1). Sequential recruitment will be followed, starting with the first SVN enrolled. A matching control neonate will then be recruited for each SVN, with the process continuing until the target sample size is achieved over a 12-month recruitment period.

The inclusion and exclusion criteria by stage are presented in Table 1.

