## Figures and Tables

**Figure 1 nutrients-16-04242-f001:**
[figure not shown]
Flow chart of the DenBalo study schedule.

**Table 1 nutrients-16-04242-t001:** Denbalo inclusion and exclusion criteria.

Step	Inclusion Criteria	Exclusion Criteria
Screening	Women between 15 and 40 years old at study inclusion. Fundal height between 24 cm and 27 cm. Women living in the health zones of Accart-Ville, Colma 1, or Farakan Women not planning to give birth or move outside the study area in the first 6 months of the infant’s life Oral consent	Fundal height <24 cm or >27 cm Women living outside the sanitary zone of the Accart-Ville, Colma 1, or Farakan Women planning to give birth outside the study area or to move from it within the first 6 months of the infant’s life
Pre-inclusion	GA between 24 weeks 1 completed day and 29 weeks 6 days (ultrasound) Monofetal pregnancy without visible malformation Women agreeing to give their informed consent to participate in the study	GA <24 weeks or ≥30 weeks (ultrasound) Multi-fetal pregnancy Malformation visible on ultrasound
Inclusion	Women seen in labor before the rupture of membranes, thus allowing vaginal sampling Delivery of a live birth Vaginal birth Absence of severe infectious pathology, severe pneumopathy, or respiratory distress in the neonate Neonates who did not receive corticosteroids or antibiotics at birth *For SVN group:* Neonates born between the 34th and 37th weeks of pregnancy Or birthweight below the 10th centile of the recommended international, sex-specific birthweight for GA standard Or birth weight ≤2500 g *For healthy control group:* Neonates born after the 37th week of pregnancy Birth weight >2500 g	Women seen in labor after rupture of membranes Cesarean delivery Neonates with severe infectious disease, severe pneumopathy, or respiratory distress Neonates who received corticosteroids or antibiotics just after birth *For SVN group:* Neonates born before the 34th week of pregnancy Birth weight <1500 g

**Table 2 nutrients-16-04242-t002:** The quality control criteria for TCD and FL assessment.

Assessments	Quality Control Criteria

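### The printed gestational-age equation cannot return 24 to 30 weeks, and the TCD and FL repeat limits that both stand for one week disagree about 14-fold

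*Protocol article*

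**What the plan says.** Protocol article, section 2.2, Step 2 (Pre-inclusion), dates every pregnancy from ultrasound measurements of TCD and FL: "GA will be calculated using the Alliance for Maternal Newborn Health Improvement (AMANHI) formula based on two best measurements". The equation that follows is, in plain notation, GA = exp[0.3825021 × ln(TCD) + 0.3321277 × ln(FL)]. No constant term appears, neither the input nor the output unit is stated with it, and one more bracket opens than closes.

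The result must fall in a fixed range. Section 2.2 says "Singleton pregnancies with GA between 24 and 29 weeks (6 days) will be eligible for pre-inclusion". Table 1 repeats the window as an inclusion rule ("GA between 24 weeks 1 completed day and 29 weeks 6 days (ultrasound") and an exclusion rule ("GA <24 weeks or ≥30 weeks (ultrasound").

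The same step sets the trigger for a third image: a difference between the two readings of "more than ±1 week of GA (i.e., >1.8 mm for TCD or >0.24 mm for FL").

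No other dating equation or repeat limit appears in the article.

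**The concern.** An equation used to admit women at 24 to 29 completed weeks has to be able to return such values, and this one does not appear to. Two limits offered as equivalents of the same week should also have a similar effect on GA when put through the equation. Instead, the FL limit is far smaller than the TCD limit, although FL is the larger dimension at these ages (assumed sizes below).

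GA carries much of the design. It decides pre-inclusion. At birth, Table 1 uses it for the preterm and below-10th-centile routes into the small vulnerable newborn (SVN) group, for the exclusion of births before the 34th week from that group, and for the term criterion in controls. The birth-weight route (2500 g or less) does not use GA. A reader who wants to reproduce or pool the GA values has only this equation in the article to work from.

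**Working it through.** **Inputs from the article:** a = 0.3825021 (ln TCD); b = 0.3321277 (ln FL); window 24 weeks to 29 weeks 6 days, i.e. 168 to 209 days; limits 1.8 mm (TCD) and 0.24 mm (FL).

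**Assumed, not in the article:** central TCD/FL of 25/43 mm at 24 weeks, 30/50 mm at 27 weeks and 35/57 mm at 30 weeks. Ranges are TCD 23–27, 27–32 and 32–38 mm, with FL 40–46, 46–54 and 53–61 mm.

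**1. Equation as printed.** At 30 and 50 mm the exponent is 0.3825021 × 3.4012 + 0.3321277 × 3.9120 = 1.3010 + 1.2993 = 2.6003, and exp(2.6003) = 13.47. With the same sizes in cm the result is 2.60.

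| Assumed GA | TCD / FL (mm) | Result, mm | Result, cm | Multiplier needed for weeks |
|---|---|---|---|---|
| 24 wk | 25 / 43 | 11.95 | 2.30 | 24/11.95 = 2.01 |
| 27 wk | 30 / 50 | 13.47 | 2.60 | 27/13.47 = 2.00 |
| 30 wk | 35 / 57 | 14.92 | 2.88 | 30/14.92 = 2.01 |

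Over the whole assumed range the result is 11.3 to 15.8 in mm, 2.2 to 3.0 in cm and 4.7 to 7.3 with one input in each unit. None of these is 24 to 30 (weeks) or 168 to 209 (days).

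**2. Does this depend on the assumed sizes?** Put FL = r × TCD. Then GA = r^b × TCD^(a+b) with a + b = 0.7146298, so TCD = (24 / r^b)^(1/0.7146298). For r = 1.4, 1.6 and 1.8, a result of 24 needs TCD of 73.0, 68.6 and 65.0 mm with FL of 102, 110 and 117 mm. Those are about twice the sizes assumed at 30 weeks. Even 60 and 80 mm give only 20.5.

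**3. What seems to be missing.** The multiplier needed is nearly the same at all three ages, which fits one lost constant: ln(2.0) ≈ 0.70 in the exponent, with a range of 0.64 to 0.76 over the assumed sizes. For output in days the factor would be about 14.

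**4. Repeat limits.** The relative change in GA is ((TCD + d)/TCD)^a × ((FL + e)/FL)^b − 1. Any constant cancels, so this step does not depend on the missing term. At 27 weeks (189 days):

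- TCD alone: 189 × [(31.8/30)^a − 1] = 4.3 days
- FL alone: 189 × [(50.24/50)^b − 1] = 0.30 day
- Ratio: about 14

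| Assumed GA | 1.8 mm TCD alone | 0.24 mm FL alone | FL change that, with 1.8 mm TCD, makes 7 days | Multiple of 0.24 mm |
|---|---|---|---|---|
| 24 wk | 4.5 d | 0.31 d | 1.9 mm | 7.8 |
| 27 wk | 4.3 d | 0.30 d | 2.2 mm | 9.0 |
| 30 wk | 4.1 d | 0.29 d | 2.4 mm | 9.9 |

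Over the assumed sizes, 1.8 mm of TCD is worth 3.8 to 4.9 days and 0.24 mm of FL 0.27 to 0.33 day. The FL change needed alongside 1.8 mm of TCD is 1.5 to 2.8 mm, or 6 to 12 times the printed limit. If FL alone had to move GA by one week, it would take 5.2 to 6.3 mm, or 22 to 26 times.

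**The case against.** The strongest reply is that the line is a transcription slip. The text names the AMANHI formula and cites reference [29], the unbalanced brackets suggest that something was lost in typesetting or in reading the PDF, and the repeat limits in the same step show that the team worked in mm. An equation that admits nobody would also have stopped pre-inclusion at the first scan, and section 2.5 has an external gynecologist regularly check the images and GA estimations. This largely stands. A reader might infer that women were misdated or assigned to the wrong group. The article does not show that, and use of the complete formula in the field is the more plausible reading. Text extraction does not readily explain the FL limit, though, since it is an ordinary figure in a sentence.

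A second reply concerns the yardstick. The limits are joined by an *or*, and taken singly the TCD limit does not make a week either (about 4 days). That is fair, and it is why the size of the FL error is given as a range. It does not rescue the pair, because two equivalents of the same week still differ about 14-fold.

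Two further inferences are tempting. One is that the FL limit should read 0.24 cm. A cm value labelled mm is a likely cause, but it is unproven without the source. The other is that a third image becomes routine. That depends on the repeatability of FL, which the article does not give. Nor is there an error in choosing images by quality: the criteria are predefined and set out in Table 2.

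**Conclusion.** As printed, the equation cannot return any GA in the eligible window in any combination of mm and cm. It falls short by a factor of about 2 if the output is weeks. This rests on assumed fetal sizes, but the margin is wide enough that no plausible choice changes it. The two repeat limits are mutually inconsistent by about 14-fold on the article's own coefficients, whatever constant is missing. The FL limit is too small by roughly 6 to 12 times on joint growth and 22 to 26 times on FL alone.

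These are errors in a dating formula and a decision threshold, not in wording alone, and they need correcting. Whether they go beyond reporting depends on which version was coded, and the article does not say. If the complete formula was used, GA was sound but cannot be reproduced from the article. Only if the printed version was used would eligibility and GA-based group assignment be affected.

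**What to change.** 1. Check the equation and the FL limit against reference [29].
2. Print the full equation with its constant, input units and output unit, with one worked example that falls inside 24 weeks to 29 weeks 6 days.
3. Print the FL limit from the source and state whether each limit represents one week of growth in that dimension or one week of calculated GA.
4. Confirm in writing that the coded equation and limits match the source. Recompute GA, and the eligibility and group status that depend on it, from the stored measurements only if the printed version was used.

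The cost is a correction to one equation and one limit, plus a check of a few lines of code. Any recomputation needs no new scans. The ranking of images by quality can stay as it is.

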### 2.3. Data Collection

Table 3 shows the overview of the time schedule and measurements of this study. Anthropometric, clinical measures and a series of biospecimen samples will be collected from women and their infants at multiple time points covering pregnancy and lactation, including 24–30 weeks, 33–34 weeks, and 36 weeks at birth, day of life (Dol) 1, 2, 3, 4, 5, 6, 7, 14, 15, 30, 60, and 180.

#### 2.3.1. Metadata

**
*Anthropometric and clinical measurements*
**

During pre-inclusion and at each visit after inclusion, anthropometric measurements from all women will be taken, and infant’s anthropometric measurements will be taken at each visit after birth. Maternal weight will be measured to the nearest 100 g with a Seca 876 scale, height to the nearest 1 cm with a ShorrBoard Infant/Child/Adult, and MUAC will be measured to the nearest 1 mm with a Seca 212 measuring tape. Infant weight will be measured to the nearest 10 g using a Seca 384 scale and height will be measured to the nearest 1 mm using a Seca 416 infantometer. Infant chest circumference and MUAC will be measured to the nearest 1 mm with a Seca 212 measuring tape. At birth, the infant’s anthropometric measurements will be taken within 6 h of birth. Measurements will be taken in duplicate, and a third measurement will be taken if there is a large discrepancy between measures (e.g., >0.3 kg for weight, >3 cm for height, and >1 cm for MUAC) between the first two measurements.

Clinical measurements (e.g., signs of fever, vomiting, diarrhea, cough, difficulty breathing, and running nose) will be taken along with the anthropometric measures at each visit. Additionally, at birth, the infant’s nutritional and health status will be assessed using the Integrated Management of Neonatal and Childhood Illness approach. Cardiovascular evaluation (APGAR score [30]) will be taken within 1 min of birth, and a neurological and physical maturity examination (Dubowitz score [31]) will be carried out within 12 h of birth.

**
*Household visit questionnaires*
**

Socioeconomic and demographic information from all participants will be collected during the first household visit (e.g., 33–34 weeks of gestation). The project sociologist will ask questions on household members’ characteristics, household possessions, household food security, and water sanitation and hygiene (WaSH), which is a framework used to assess the quality and accessibility of water sanitation and hygiene facilities and services. A diet quality survey will be used to assess the dietary diversity of the women.

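### The only stated limits for a third anthropometric reading suit adult measurement, not newborns: infant weight duplicates may differ by 0.3 kg, across the 2500 g group cut-off, without a repeat.

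*Protocol article*

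**What the plan says.** Section 2.3.1 (Anthropometric and clinical measurements) describes the maternal instruments, then the infant instruments, then the timing at birth, and closes with one repeat rule.

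- Mothers: "Maternal weight will be measured to the nearest 100 g with a Seca 876 scale, height to the nearest 1 cm".
- Infants: "Infant weight will be measured to the nearest 10 g using a Seca 384 scale and height will be measured to the nearest 1 mm", and "Infant chest circumference and MUAC will be measured to the nearest 1 mm with a Seca 212 measuring tape".
- Timing: "At birth, the infant’s anthropometric measurements will be taken within 6 h of birth".
- Rule, in the next sentence: "Measurements will be taken in duplicate, and a third measurement will be taken if there is a large discrepancy between measures". The limits, offered as examples, are ">0.3 kg for weight, >3 cm for height, and >1 cm for MUAC".

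No limits are given for infants alone, and none for chest circumference, which is measured only in infants. Table 1 uses birth weight to form the groups. One of three routes into the SVN group is "Or birth weight ≤2500 g". The other two are birth weight below the 10th centile for gestational age and birth between the 34th and 37th weeks. Controls must weigh more than 2500 g, and SVNs below 1500 g are excluded. Table 3 schedules infant anthropometry daily from birth to day 7 and again on days 14, 15, 30, 60 and 180.

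**The concern.** Duplicate readings protect against reading and recording slips only if the limit for a repeat is small compared with the errors that matter. The weight and height limits look reasonable for an adult. Applied to a newborn of about 2.5 kg, they leave a wide band of error in which two clearly discordant readings are accepted.

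Two uses of the data are exposed. Birth weight decides or helps to decide SVN or control status, and it cannot be measured again once the 6-hour window has passed. The daily weights of the first week are meant to show changes that are small beside 0.3 kg. Section 2.2 shows the better practice in the same article: its repeat limits for ultrasound are tied to a stated tolerance of one week of gestational age. The anthropometric limits are tied to nothing that is stated.

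**Working it through.** The plan gives no figure to reproduce here, so the check compares the limits with the plan's own resolutions and cut-offs.

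**Inputs from the protocol article.** Limits 300 g, 30 mm and 10 mm (Section 2.3.1). Infant resolution 10 g, 1 mm and 1 mm; maternal resolution 100 g, 1 cm and 1 mm (same section). Weight thresholds 2500 g and 1500 g (Table 1).

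**Assumed, not in the documents.** SD *s* of a single infant weight reading, 10 to 150 g. Infant weight gain after the first days, 20 to 40 g/day.

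**1. Limit divided by resolution**
- Maternal weight 300/100 = 3; maternal height 3 cm/1 cm = 3.
- Infant weight 300/10 = 30; infant length 30/1 = 30.
- MUAC 10/1 = 10 for infants and also for mothers, so this ratio alone does not separate the two.

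**2. Limit as a share of the weight thresholds**
- 0.3/2.5 = 12%; 0.3/1.5 = 20%.

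**3. Largest error in an accepted pair**
- If one reading is right and the two differ by 300 g, their mean is wrong by 300/2 = 150 g, which is 6% of 2500 g.
- Example: 2360 g and 2650 g differ by 290 g, so no third reading is taken. They lie on opposite sides of 2500 g. If they are averaged (an assumption, since the text does not say), the result is 5010/2 = 2505 g, on the control side of the weight cut-off.

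**4. How often the rule would fire on error-free technique.** The difference of two independent readings has SD *s*√2, so P(third reading) = 2[1 − Φ(300/(*s*√2))].
- *s* = 50 g: about 0.00002.
- *s* = 75 g: 0.5%.
- *s* = 100 g: 3.4%.
- *s* = 150 g: 15.7%.
- For a 5% rate, *s* must be 300/(1.96√2) = 108 g. For length the same formula gives 10.8 mm, and for MUAC 3.6 mm.

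**5. Chance that one gross slip *g* passes.** With *s* = 10 g this is Φ((300 − *g*)/(10√2)); the other tail is negligible.
- *g* = 100 to 250 g: about 1.00.
- *g* = 290 g: 0.76.
- *g* = 300 g: 0.50.
- *g* = 350 g: about 0.

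**6. Against growth.** At 20 to 40 g/day, 300 g equals 7.5 to 15 days of gain, and a 150 g error in the mean equals 3.75 to 7.5 days.

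**The case against.** Several points on the other side carry weight.

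- *The limits are examples and may be meant for mothers.* They are introduced as examples, the weight and height values are exactly 3 times the maternal resolution, and chest circumference has none. A condensed article may also omit infant limits held elsewhere. But the rule follows directly on the sentence about newborns, the section also uses the word height for infant length, and no other limits are stated. If only mothers were meant, the text still needs correcting.
- *Other checks exist.* Section 2.5 has validation codes, weekly checks and queries to the field, and the daily series may expose an isolated outlier. This stands, so it would be wrong to infer that gross errors go wholly unchecked or that duplicates give no protection: differences above 0.3 kg do trigger a repeat. But 2360 g and 2650 g are both plausible newborn weights, and a later query cannot recover a birth weight.
- *The effect on grouping is probably slight.* With an assumed birth weight mean of 3.05 kg and SD of 0.42 kg (9.5% below 2500 g, within the 8–11% in the Introduction), the density at 2500 g is 0.403 per kg. If every pair had an error in the mean spread evenly over ±0.15 kg, 0.403 × 0.075 = 3% of births would cross. If 1 to 5% of pairs had such an error (assumed), that is 0.03 to 0.15% of births, or 0.04 to 0.2 of 141 infants. Fivefold enrichment near the cut-off would make it about one infant at most. Some would also remain SVN through the centile or gestational-age route. This objection limits the size of the point.
- *The three objectives concern microbiota, immunity and milk.* True, but the groups being compared are formed partly by birth weight.

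**Conclusion.** The point holds as a weakness in a stated rule. On the article's own figures, the only limits given are 30 times the infant resolution for weight and length and 10 times for MUAC, and 0.3 kg is 12% of the group cut-off. Followed as written, the duplicate rule does not catch infant weight discrepancies up to 0.3 kg. It is worth correcting because the change is cheap and birth weight cannot be measured again.

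A reader might infer that about 12% of births risk being put in the wrong group. Under the distribution assumed above, that is the share within 0.15 kg of 2500 g: Φ((2.65 − 3.05)/0.42) − Φ((2.35 − 3.05)/0.42) = 0.170 − 0.048 = 0.12. It is not a misclassification rate. Such a rate depends on how often gross errors occur, which the documents do not give, and weight is only one of three SVN routes.

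The conclusion assumes that the stated limits apply to infants. The effect on grouping further assumes that the duplicate study weight assigns the group and that duplicates are averaged; the text states neither.

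**What to change.** In Section 2.3.1:

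1. Keep the present limits for mothers and say that they are maternal.
2. Add separate, tighter infant limits for weight, length, MUAC and chest circumference, based on infant measurement error. Values of about 50 g for weight, 7 mm for length and 5 mm for MUAC and chest circumference would illustrate the scale. They do not come from the documents and should be confirmed from the study's own standardisation data. By the formula above, they would prompt a third reading in 5% of honest pairs at a reading SD of 50/(1.96√2) = 18 g, 7/(1.96√2) = 2.5 mm and 5/(1.96√2) = 1.8 mm.
3. State how readings are combined, for example the mean of the two closest, and that this birth weight is the one used for Table 1.
4. Program the limits as an immediate tablet check, so that the repeat is taken while the infant is present.

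The cost is a short addition to the text, a changed validation rule, and a few more third readings of perhaps one or two minutes each.
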